### 3. Background

**a) Describe past experimental and/or clinical findings leading to the formulation of the study.**

A randomized controlled pilot study here at Stanford for colorectal surgery patients demonstrated better physical function and lower pain scores at 30 days after surgery in case of prehabilitation program.

However, prehab programs are still not common in practice. Major impediments include the lack of patient compliance.

So, we would like to compare compliance of personalized health optimization program with one-on-one coaching, tailored to each patient's predicted surgical recovery (SURGE program) vs. a less-intensive approach.

**b) Describe any animal experimentation and findings leading to the formulation of the study.**

none.

### 4. Radioisotopes or Radiation Machines

**a) List all standard of care procedures using ionizing radiation (radiation dose received by a subject that is considered part of their normal medical care). List all research procedures using ionizing radiation (procedures performed due to participation in this study that is not considered part of their normal medical care). List each potential procedure in the sequence that it would normally occur during the entire study. More Info**

| Identify Week/Month of study | Name of Exam | Identify if SOC or Research |
|------------------------------|--------------|-----------------------------|
|------------------------------|--------------|-----------------------------|

**b) For research radioisotope projects, provide the following radiation-related information:**

**Identify the radionuclide(s) and chemical form(s).**

**For the typical subject, provide the total number of times the radioisotope and activity will be administered (mCi) and the route of administration.**

**If not FDA approved provide dosimetry information and reference the source documents (package insert, MIRD calculation, peer reviewed literature).**

**c) For research radiation machine projects, provide the following diagnostic procedures:**

**For well-established radiographic procedures describe the exam.**

**For the typical subject, identify the total number of times each will be performed on a single research subject.**

**For each radiographic procedure, provide the setup and technique sufficient to permit research subject dose modeling. The chief technologist can usually provide this information.**

---

**Title :** Immune system modulation by enhanced vs standard prehabilitation program in patients undergoing elective major surgery - a prospective monocentric randomized single-blinded control . . .

**Approval Period:** 10/23/2023 - 12/31/2999

---

**For radiographic procedures not well-established, provide FDA status of the machine, and information sufficient to permit research subject dose modeling.**

**d) For research radiation machine projects, provide the following therapeutic procedures:**

**For a well-established therapeutic procedure, identify the area treated, dose per fraction and number of fractions. State whether the therapeutic procedure is being performed as a normal part of clinical management for the research participants' medical condition or whether it is being performed because the research participant is participating in this project.**

**For a therapeutic procedure that is not well-established, provide FDA status of the machine, basis for dosimetry, area treated, dose per fraction and number of fractions.**

## 5. Devices

- a) Please list in the table below all Investigational Devices (including Commercial Devices used off-label) if they are being studied.
- b) Please list in the table below all IDE Exempt Devices (Commercial Device used according to label, Investigational In Vitro Device or Assay, or Consumer Preference/Modifications/Combinations of Approved Devices) to be used on participants.

## 6. Drugs, Reagents, or Chemicals and Devices

- a) Please list in the table below all investigational drugs, reagents or chemicals if they are being studied.
- b) Please list in the table below all commercial drugs, reagents or chemicals if they are being studied.

## 7. Medical Equipment for Human Subjects and Laboratory Animals

**If medical equipment used for human patients/participants is also used on animals, describe such equipment and disinfection procedures.**

none

## 8. Participant Population

- a) **State the following: (i) the number of participants expected to be enrolled at Stanford-affiliated site(s); (ii) the total number of participants expected to enroll at all sites; (iii) the type of participants (i.e. students, patients with certain cancer, patients with certain cardiac condition) and the reasons for using such participants.**

(i) 120 patient participants total from Stanford Health Care. 15 surgeons from SHC.  
(ii) total = 120 participants (only one site included in this study). 15 surgeons from SHC  
(iii) participants will be patients undergoing elective major surgery. Reasons for using this group of patients is that they have a baseline significant risk of post-operative complications including surgical site infections

**Title :** Immune system modulation by enhanced vs standard prehabilitation program in patients undergoing elective major surgery - a prospective monocentric randomized single-blinded control . . .

**Approval Period:** 10/23/2023 - 12/31/2999

and readmissions. Finally, patients undergoing major abdominal surgery often feel overwhelmed, or a sense of loss of control over their bodies; therefore, we hope that this intervention would help support them and also give them a sense of agency in their own recovery and health.

**b) State the age range, gender, and ethnic background of the participant population being recruited.**

Age range: 18 or older

Gender: representative of the patient population of Stanford Health Care

Ethnic background: representative of the patient population of Stanford Health Care

**c) State the number and rationale for involvement of potentially vulnerable subjects in the study (including children, pregnant women, economically and educationally disadvantaged, decisionally impaired, homeless people, employees and students). Specify the measures being taken to minimize the risks and the chance of harm to the potentially vulnerable subjects and the additional safeguards that have been included in the protocol to protect their rights and welfare.**

Economically disadvantaged people will be able to take part in the study as it will not cost them anything to participate.

For educationally disadvantaged people who wish to take part in the program, we will determine which aspects of the program they would be able to do, based on their ability level. We will also ask patients' caregivers if they are able to help the patients with the program.

Decisionally impaired patients will not be included in the study.

Employees and students will be given the opportunity to participate, but will be explicitly assured that their decision to participate or not participate will have no bearing on their professional or educational status.

Children and pregnant women will not be enrolled.

**d) If women, minorities, non-English speaking individuals, or children are not included, a clear compelling rationale must be provided (e.g., disease does not occur in children, drug or device would interfere with normal growth and development, etc.).**

Children will not be included as children typically do not undergo these types of abdominal operations, and this study is being performed only in the adult surgery clinic.

**e) State the number, if any, of participants who are laboratory personnel, employees, and/or students. They should render the same written informed consent. If payment is allowed, they should also receive it. Please see Stanford University policy.**

If any eligible patients happen to also be laboratory personnel, employees, and/or students, and are interested in the study, then they may be included. They will go through the same RedCap informed consent process as other patients. Payment will not be given for these patients.

**f) State the number, if any, of participants who are healthy volunteers. Provide rationale for the inclusion of healthy volunteers in this study. Specify any risks to which participants may possibly be exposed. Specify the measures being taken to minimize the risks and the chance of harm to the volunteers and the additional safeguards that have been included in the protocol to protect their rights and welfare.**

None of the participants are healthy volunteers.

**g) Describe your plan to identify and recruit potential participants including who will inform them about the study and how they will be initially contacted by the researchers (e.g., <https://med.stanford.edu/spectrum/researcher-resources/participant-engagement/engagement-consultations.html> Participant Engagement services; chart review; treating physician; ads including social media posts). All final or revised recruitment materials must be approved by the IRB before use. Contacting potential participants is not permitted prior to IRB approval. See <https://stanfordmedicine.box.com/shared/static/8uebsdjrrqjyauanjp9i9d0gm1i480co.pdf> Recruitment Guidance for additional information.**

Chart review by the PI will be performed to determine potential subjects coming into the outpatient surgery clinic. Surgeons, nurse practitioners, physician assistants, and nurses who are directly taking care of the patient will ask eligible patients during that surgical consultation visit whether they are interested in enrolling/hearing more about the study. If they are, they will be referred to the research staff who will either

**Title :** Immune system modulation by enhanced vs standard prehabilitation program in patients undergoing elective major surgery - a prospective monocentric randomized single-blinded control . . .

**Approval Period:** 10/23/2023 - 12/31/2999

enroll them in person or over the phone.

**h) Inclusion and Exclusion Criteria.**

**Identify inclusion criteria.**

Adult patients aged  $\geq 18$  years undergoing major elective surgeries, under general anaesthesia (e.g., colon or colorectal resection, partial or total gastrectomy, pancreaticoduodenectomy, hepatectomy, cystectomy or major gynecologic, thoracic, plastic and neurosurgeries)

**Identify exclusion criteria.**

Children ( $<18$  years), patients undergoing emergency or urgent surgery  
Patients undergoing surgery in  $<28$  days, non-english speakers will not be included. Premorbid conditions or orthopedic impairments that contraindicated physical exercise, cognitive disabilities, ASA score 4 or higher or patient under palliative care, expected length of stay at hospital  $< 48$  hours and no access to internet will be also criteria of non inclusion.

**i) Describe your screening procedures, including how qualifying laboratory values will be obtained. If you are collecting personal health information prior to enrollment (e.g., telephone screening), please request a waiver of authorization for recruitment (in section 15).**

Screening will be performed by the PD who will screen the electronic medical records of the patients to be seen in the clinics of the colorectal surgeons to identify potential participants. A waiver of authorization for recruitment will be requested.

**j) Describe how you will be cognizant of other protocols in which participants might be enrolled. Please explain if participants will be enrolled in more than one study.**

We will ask the patients if they are in any other protocols (except the protocol IRB #46978 in which they could be included). They will be allowed to be enrolled in other studies as long as they do not interfere with this study (for example, they may be enrolled in Tissue Bank or GenePool, but not in any other rehabilitation, diet, or exercise studies).

**k) Payment/reimbursement. Explain the amount and schedule of payment or reimbursement, if any, that will be paid for participation in the study. Substantiate that proposed payments are reasonable and commensurate with the expected contributions of participants and that they do not constitute undue pressure on participants to volunteer for the research study. Include provisions for prorating payment. See payment considerations**

There will be no monetary compensation for the study.

**l) Costs. Please explain any costs that will be charged to the participant.**

There will be no costs that will be charged to the participants.

**m) Estimate the probable duration of the entire study. Also estimate the total time per participant for: (i) screening of participant; (ii) active participation in study; (iii) analysis of participant data.**

Probable duration of the entire study: 6 months

Per participant:

(i) screening: 15 minutes

(ii) active participation in study: 90 days

(iii) analysis of data: 1 hour

## 9. Risks

- a) For the following categories include a scientific estimate of the frequency, severity, and reversibility of potential risks. Wherever possible, include statistical incidence of complications and the mortality rate of proposed procedures. Where there has been insufficient time to accumulate significant data on risk, a statement to this

**Title :** Immune system modulation by enhanced vs standard prehabilitation program in patients undergoing elective major surgery - a prospective monocentric randomized single-blinded control . . .

**Approval Period:** 10/23/2023 - 12/31/2999

effect should be included. (In describing these risks in the consent form to the participant it is helpful to use comparisons which are meaningful to persons unfamiliar with medical terminology.)

**The risks of the Investigational devices.**

None

**The risks of the Investigational drugs. Information about risks can often be found in the Investigator's brochure.**

none

**The risks of the Commercially available drugs, reagents or chemicals. Information about risks can often be found in the package insert.**

none

**The risks of the Procedures to be performed. Include all investigational, non-investigational and non-invasive procedures (e.g., surgery, blood draws, treadmill tests).**

Investigational and procedures: Physical therapy and surveys. The risk associated with these procedures is low to null as the study protocol involves exercises to be done only at the comfort level of the patient. Blood draws will be collected by licensed personnel using sterile supplies and aseptic technique (as validated by the IRB-#46978 )

Non-investigational: elective surgery and associated post-operative care, and pre-operative testing. The risk of these procedures varies according to the procedure and the patient, but are not expected to increase as a result of the study activities.

**The risks of the Radioisotopes/radiation-producing machines (e.g., X-rays, CT scans, fluoroscopy) and associated risks.**

none

**The risks of the Physical well-being.**

There are minimal risks to the physical well-being of the participants, as the study protocol involves exercises to be done only at the comfort level of the patient, and well-accepted dietary, cognitive or well-being recommendations.

**The risks of the Psychological well-being.**

There are minimal risks to the psychological well-being of the participants.

**The risks of the Economic well-being.**

There are no risks to the economic well-being of the participants as the study protocol will not incur additional costs to the patients.

**The risks of the Social well-being.**

There are no risks to the social well-being of the participants as the study protocol will not involve their social situation.

- b) **If you are conducting international research, describe the qualifications/preparations that enable you to both estimate and minimize risks to participants. Provide an explanation as to why the research must be completed at this location and complete the International Research Form. If not applicable, enter N/A.**

none

- c) **Describe the planned procedures for protecting against and minimizing all potential risks. Include the means for monitoring to detect hazards to the participant (and/or to a potential fetus if applicable). Include steps to minimize risks to the confidentiality of identifiable information.**

Administration of frequent surveys to detect increase in stress and pain levels will monitor for hazards. Also, patients will be closely monitored in the post-operative inpatient period for any physical problems.

The confidentiality of identifiable information will be protected as only the members of the study staff will

**Title :** Immune system modulation by enhanced vs standard prehabilitation program in patients undergoing elective major surgery - a prospective monocentric randomized single-blinded control . . .

**Approval Period:** 10/23/2023 - 12/31/2999

have access to the information, and the data will be stored on a secure computer (the PI's computer) which is password protected, encrypted by Stanford IT, and located in a locked office in a building under 24-hour surveillance.

- d) Explain the point at which the experiment will terminate. If appropriate, include the standards for the termination of the participation of the individual participant Also discuss plans for ensuring necessary medical or professional intervention in the event of adverse effects to the participants.**

The study poses only a small risk to participants. There is no plan to discontinue the study before all participants have been enrolled and samples have been collected. Drs. [name] and [name] will be available in the unlikely event that a participant needs medical attention as a result of study participation.

Individual participants may be terminated from the study if they choose to no longer be in the study.

In the event of adverse effects to the participants, the study staff will ensure that they receive the necessary medical and professional intervention.

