## 2. Study Procedures

**a) Please SUMMARIZE the research procedures, screening through closeout, which the research participant will undergo. Sections in the protocol attached in section 16 can be referenced, BUT do not copy the clinical protocol. Be clear on what is to be done for research and what is part of standard of care. For research involving collaborators, please specify the respective roles of Stanford and each collaborator on the protocol.**

Standard prehabilitation:

Patients will be provided with standard instructions in a hard-copy form specific to prehabilitation before surgery associating physical, nutritional, stress-reduction and cognitive recommendations without any personalized coaching for at least 3 weeks prior to surgery (see attached ControlGroup\_ProgramBook document).

Research Activities:

---

**Title :** Immune system modulation by enhanced vs standard prehabilitation program in patients undergoing elective major surgery - a prospective monocentric randomized single-blinded control . . .

**Approval Period:** 10/23/2023 - 12/31/2999

---

1. Screening: The research team will identify eligible patients by screening the clinic schedules of general surgeons.

2. Study Enrollment: Either in person during their surgical clinic visit, or by phone at least 28 days before surgery. If patients accept to be included, they will be randomized.

3. Baseline assessment (Day 0): Nutritional (using the Mediterranean Diet Scale), physical (by measuring 6 min walk test, Timed up and go, Five Times Sit to Stand Test and Wall Squat Tests), cognitive (using the qMCI test), anxiety (using the APAIS scale and the Pain Catastrophizing Scale) and quality of life status (using the SF36-scale) at baseline (prior to prehabilitation) will be recorded on RedCap by a personnel previously trained to the achievement of tests of the study.

4. Prehabilitation: SURGE or standard program will be proposed to the patients for 3-6 weeks.

SURGE consists in a 6-session (over 3-6 weeks) personalized prehabilitation program. This program will be delivered remotely with 2 in person (with a trained member of the research team) sessions every week. Self-exercises will be promoted every day.

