>> Cognition component: participants will have the opportunity to make a personalized plan for improving their cognition with a member of the research team (SURGE). It will consist on the daily use of Lumosity training program (<https://www.lumosity.com/>), an already existing free of charge app built to increase memory skills and used in the perioperative context. The program proposed by Lumosity is tailored to each patient. The use of Lumosity will be monitored at each in person session. Patients will be expected to complete at least three 5 minute sessions of Lumosity training per day. No information will be collected by the company.

>> Stress-reduction component: participants will have the opportunity to learn techniques for mindfulness that have been established to reduce stress and assist with pain management with a member of the research team (SURGE). Patients will be offered to listen to audio recording of relaxation sessions. Each session contains a relaxation technique that the patient practices while listening to the recording. Then the technique is used the next as a baseline to introduce a new technique more advanced. For some patients who struggle with the techniques the program will be adapted. Patients will choose with 2 or 3 techniques and work on them.

5. Every 7 days, whatever the arm, a compliance questionnaire will be filled by phone, by trained members of the research team blinded to the treatment arm of the study and collected in RedCap

6. End of prehabilitation program: Nutritional (using the Mediterranean Diet Scale), physical (by measuring 6 min walk test, Timed up and go, Five Times Sit to Stand Test and Wall Squat Test), cognitive (using the qMCI test), anxiety (using the APAIS scale and the Pain Catastrophizing Scale) and quality of life status (using the SF36-scale) at the end of the prehabilitation program will be recorded on RedCap by a personnel previously trained to the achievement of tests of the study.

7. Surgery

8. Post-operative period:

>> From surgery end to discharge from the hospital, length of stay, pain and adverse clinical events will be measured and recorded on RedCap.

>> Cognitive function (using qMCI), neuropathic pain (using the DN-4 scale) and quality of life (using SF-36 scale) will be assessed 30 days after surgery and recorded on RedCap.

**b) Explain how the above research procedures are the least risky that can be performed consistent with sound research design.**

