- > Adherence to prehab programs using a modified "Rehabilitation Adherence Measure for Athletic Training" scale
- > Physical status assessment including 6 Minute Walk Test (6MWT), Timed Up and Go (TUG), Five Times Sit to Stand Test & Wall Squat Test and Body Mass Index (BMI)
- > Prevalence and global severity of anxiety using questionnaires such as the APAIS (Amsterdam Preoperative Anxiety and Information Scale) and the Pain catastrophization scale.
- > Cognitive status evaluated by the qMCI

We will also evaluate the effect of prehab programs on post-operative outcomes by collecting:

- > Hospital length of stay
- > Readmission within 30 days after surgery
- > Postoperative complications scored by the Comprehensive Complication Index (CCI) within 90 days after surgery
- > Inpatient opioid use and pain levels during hospitalization
- > Neuropathic pain, quality of life and cognitive function assessed 30 days after surgery (in comparison to before surgery)

If the intervention is found to be clearly harmful then the study will be terminated before the total projected participant population has been enrolled. This will be determined by assessing for increase in complication rates after surgery beyond our baseline rates of complications (as determined by NSQIP data). These rates will be

**Title :** Immune system modulation by enhanced vs standard prehabilitation program in patients undergoing elective major surgery - a prospective monocentric randomized single-blinded control . . .

**Approval Period:** 10/23/2023 - 12/31/2999

calculated on a quarterly basis.

The study will end after complete enrollment (120 patients) or after 16 months of enrollment into the prehab intervention if no important differences are detected.

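### The protocol relies on frequent stress and pain surveys that its schedule does not contain, and it states no recording by arm of adverse events during the 3-6 week programme

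*Protocol*

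**What the plan says.** Section 9 (Risks), item c of the protocol asks how hazards to participants will be detected. It answers with two measures. The first is: "Administration of frequent surveys to detect increase in stress and pain levels will monitor for hazards". The second is that "patients will be closely monitored in the post-operative inpatient period for any physical problems".

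The procedures are in section 2, item a:

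- **Exposure (step 4):** "SURGE or standard program will be proposed to the patients for 3-6 weeks".
- **Day 0 (step 3):** "anxiety (using the APAIS scale and the Pain Catastrophizing Scale) and quality of life status (using the SF36-scale) at baseline (prior to prehabilitation"), together with diet, physical and cognitive tests.
- **During the programme (step 5):** "Every 7 days, whatever the arm, a compliance questionnaire will be filled by phone". The callers are trained staff blinded to arm.
- **End of programme (step 6):** "anxiety (using the APAIS scale and the Pain Catastrophizing Scale) and quality of life status (using the SF36-scale) at the end of the prehabilitation" programme, again with the diet, physical and cognitive tests.
- **After surgery (step 8):** "From surgery end to discharge from the hospital, length of stay, pain and adverse clinical events will be measured and recorded on RedCap". Neuropathic pain, cognition and quality of life follow at 30 days.

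Section 2, item g allows the trial to stop early for harm: "This will be determined by assessing for increase in complication rates after surgery beyond our baseline rates of complications". The baseline rates are taken from NSQIP data and the review is quarterly.

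**The concern.** Section 9c makes a positive statement about safety monitoring, and the schedule should bear it out. Of its two measures, post-operative inpatient monitoring begins after the intervention is over. That leaves the frequent surveys as the only stated means of detecting hazards while patients are exercising, and the schedule shows none that is described as asking about stress or pain between the two programme visits.

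The protocol itself recognises that the programme can cause harm before surgery. Section 2b says that tailoring the exercises lowers the risk of injury. The exercise component in section 2a includes a fall-risk evaluation and allows the plan to be changed or stopped according to response. Section 8h excludes patients for whom exercise is contraindicated.

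Two things are at stake. The trial may be unable to report or compare between arms the events that arise during the intervention. And the quarterly harm review would see a pre-operative injury only if it also raised the rate of complications after surgery. An analysis plan cannot repair this, because events that were never recorded cannot be analysed.

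**Working it through.** The protocol gives no figure to reproduce here. The check sets section 9c, the schedule and the harm review side by side and counts assessments.

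**1. Length of the exposure window.** Section 2a, step 4 gives 3 to 6 weeks: 3 × 7 = 21 days to 6 × 7 = 42 days per patient. With the planned 120 patients all completing, that is 120 × 21 = 2,520 to 120 × 42 = 5,040 patient-days over both arms.

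**2. What is scheduled, and when.**

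| Instrument or record | Day 0 | Between the two visits | End of programme | After surgery |
|---|---|---|---|---|
| APAIS, Pain Catastrophizing Scale | yes | none | yes | none stated |
| SF-36 | yes | none | yes | 30 days |
| Walk, Timed Up and Go, sit-to-stand, wall squat | yes | none stated for both arms | yes | none stated |
| Compliance questionnaire | – | every 7 days, both arms | – | – |
| Pain and adverse clinical events | none stated | none stated | none stated | surgery end to discharge |
| Complications (CCI) | – | – | – | to 90 days |

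The named stress-related scales are therefore given twice before surgery, 21 to 42 days apart, and not at all in between. The weekly call occurs about 21/7 = 3 to 42/7 = 6 times per patient, or roughly 120 × 3 = 360 to 120 × 6 = 720 calls in all. It is described only as a measure of compliance.

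**3. What the harm review can see.** Section 2g uses complication rates after surgery. The health information listed in section 11, item b includes survey results and surgical complications, but no injury or event related to the programme. Neither supplies a route by which an event before surgery enters the review.

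**4. What is measured.** Both arms repeat the physical, anxiety, catastrophizing and quality-of-life measures at the end of the programme. Section 2g compares physical, anxiety and cognitive status before and after the programme between arms. A net decline in function or rise in anxiety would show up by arm among patients who attend that visit. Two things would not: discrete events during the programme, and harm in patients who stop or do not attend.

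**5. Contact by arm.** The weekly blinded call reaches both arms. SURGE patients also have sessions with a member of the research team who follows their response. Controls receive printed recommendations without coaching. With no fixed harm questions, spontaneous reports have more chances to surface in SURGE.

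**The case against.** The strongest reply is that this is minimal-risk research, that exercise is kept within the patient's comfort (section 9a), and that participants are not left unattended. SURGE patients are followed at coaching sessions, physicians are available, and staff are to arrange care for any adverse effect (section 9d). Section 2a is also a requested summary, and the compliance scale is an attachment that is not shown. Its items may already ask about pain or symptoms.

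Part of this stands. The care provisions bear on participant protection, but none of them says that an event is recorded or compared by arm. If the compliance scale has harm items, the sponsor can say so and much of the gap closes. The schedule, however, is not merely silent: it states a recording window for adverse events, and that window begins after the exposure ends.

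A reader might infer more than the text supports:

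- **That harms of the intervention go unmeasured altogether.** They do not, since end-of-programme function and anxiety are compared between arms.
- **That pain is never measured before surgery.** SF-36 is given twice before surgery and its items are not shown, so this cannot be asserted.
- **That neuropathic pain is assessed only at day 30.** Section 2g describes a comparison with the pre-operative state, which implies an earlier assessment, even though section 2a schedules none.
- **That events would be noticed only in SURGE.** The weekly call reaches both arms. The contact is unequal, but it is not confined to one arm.
- **That a number of missed events can be given.** The documents contain no rate of programme-related events to support one.

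**Conclusion.** The point holds in a limited form. Section 9c describes frequent surveys of stress and pain. The schedule has the relevant scales at two visits, 3 to 6 weeks apart, and a weekly questionnaire described only as compliance. Stated adverse-event recording leaves out the whole 21 to 42 days of exposure, and the harm review looks only at complications after surgery. Discrete events during the programme, and harm in patients who miss the end-of-programme visit, are therefore not recorded by arm. Informal reports may also be unequal between arms.

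This rests on taking the step 5 call at its description and on no other document adding pre-surgical adverse-event collection. It should be fixed, but it is not critical: the documented risk is low, no stated efficacy endpoint depends on it, and contact with both arms is already in place.

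**What to change.** Reconcile section 2a (steps 3 to 8), section 2g and section 9c:

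1. Add a short fixed block to the 7-day call, identical in both arms: any fall, injury or new symptom since the last call, plus brief ratings of pain and stress. Word the items without reference to coaching sessions, so that callers stay blinded. If the compliance scale already has such items, say so in section 2a.
2. Start adverse-event recording at randomisation (Day 0 at the latest) instead of at the end of surgery. Also record the reason when a patient stops the programme or misses the end-of-programme visit.
3. Tabulate pre-surgical events by arm in the quarterly review, alongside post-operative complications.
4. Reword section 9c to describe what the schedule then contains.

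The cost is slightly longer calls (about 3 to 6 per patient, already planned), a REDCap form change and an IRB modification. No new visit is needed.
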